### Power calculation

In relation to long-term health effects of initiation (or termination) of the fortification, analyses including continuous outcomes, such as BMI, will not present power problems. For incidence of obesity, fractures and T1D, calculating the least detectable excess risk is relevant. The power calculation is done generically in a worst-case scenario using a dichotomous outcome with a low prevalence. The least detectable excess risk is calculated assuming that either one (at least 50,000 individuals) or two birth cohorts are included. As the follow-up period varies, the final prevalence (= incidence × duration) will be used and varied from 1-8%. The significance level is α = 0.05 and power β = 0.80. Table 1 shows the least detectable relative risk of outcome after change in fortification.

**Table 1 T1:** Least detectable relative risk of outcomes in relation to exposure to foods fortified with vitamin D

**N (exposed/non-exposed)**	**Prevalence of outcome (fractures, T1D, obesity)**				
	**0.5%**	**1%**	**2%**	**4%**	**8%**
50,000/50,000	1.27	1.19	1.13	1.09	1.07
100,000/100,000	1.19	1.13	1.09	1.07	1.05

For analyses using DBSs, power calculations were performed under 3 scenarios related to the fraction of the exposure variance explained including covariates: no adjustment, 30% explained or 60% explained. Table 2 gives the least detectable hazard ratios (for fractures and diabetes) or odds ratios (for BMI) of outcome related to 1 SD difference in 25(OH)D3 for a sample size of 1000 cases and 1000 controls using α?=?0.05 and β?=?0.80.

**Table 2 T2:** Least detectable hazard ratios (for fractures and diabetes) or odds ratios (for BMI) of outcome related to 1 SD difference in 25(OH)D3 for a sample size of 1000 cases and 1000 controls

**Least detectable Hazard (HR) or Odds rate (OR) ratios related to 1 SD difference in 25(OH)D3**	**1000 cases (obesity, diabetes or fractures) and 1000 time- and gender-matched controls**		
	**No covariates**	**30% variance explained**	**60% variance explained**
OR ratio	1.13	1.16	1.22
HR ratio	1.09	1.11	1.15

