#### Childhood overweight and obesity

The Copenhagen School Health Record Registry (CSHRR) includes every student attending a primary school in Copenhagen Municipality since birth in year 1930 through 1990 and comprises more than 370,000 records, which have been computerized for research purposes [22-24]. Overweight and obesity will be calculated from weight and height, which were measured at age 6–7 and at age 13–14 throughout the time period, but also annually until 1984. The CSHRR comprises approx. 10% of all Danes from each birth cohort. Birth weight, birth complications, gestational diabetes, pre-pregnancy weight and gestational and maternal age are retrievable from the National Medical Birth Registry. Data are available from 1973 onward.

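### Table 1 lists obesity under 50,000 or 100,000 per group, but the only obesity source described holds about 10% of each birth cohort, so power for dichotomous obesity at the stated relative risks is about 14–20.5%

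*Protocol article*

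**What the plan says.** The Power calculation section sets BMI aside as a continuous outcome without power problems and then turns to dichotomous outcomes: "For incidence of obesity, fractures and T1D, calculating the least detectable excess risk is relevant". It describes the method as follows: "The power calculation is done generically in a worst-case scenario", the scenario being a yes/no outcome of low prevalence. Group size is fixed by "assuming that either one (at least 50,000 individuals) or two birth cohorts are included", and the error rates by "The significance level is α = 0.05 and power β = 0.80". Table 1 has two rows, 50,000/50,000 and 100,000/100,000, under a column heading that begins "Prevalence of outcome (fractures, T1D, obesity". No other calculation for obesity in the fortification comparisons is given.

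Under Databases, the section Childhood overweight and obesity takes weight and height from the Copenhagen School Health Record Registry (CSHRR). It reports more than 370,000 records for birth years 1930 through 1990 and states: "The CSHRR comprises approx. 10% of all Danes from each birth cohort". The article describes no nationwide or adult source for obesity. Statistical analyses plans linear regression for BMI and logistic regression for overweight and obesity as categories, both comparing birth cohorts.

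**The concern.** Table 1's group sizes are whole national birth cohorts. Fractures, from a national patient register, and T1D, from a national childhood register, can in principle use them. Obesity, as described, cannot, because its register covers one municipality.

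Obesity is one of the three outcomes of the first phase. Under Implications, the article expects its results to inform the decision on resuming fortification. If a null result for obesity were set against Table 1, it would seem to speak against relative risks of 1.05 to 1.27, most of which the available records would usually miss.

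**Working it through.** **Inputs**
- Two-sided α = 0.05 and power 0.80 (Power calculation). Sidedness is not stated; two-sided is confirmed by the reproduction in step 1.
- Prevalence 0.5, 1, 2, 4 and 8% (Table 1), taken as the risk in the reference group.
- Table 1 group sizes: 50,000 and 100,000 per group.
- Register share: about 10% of each birth cohort (Childhood overweight and obesity).
- Register total: more than 370,000 records over 1930–1990, which is 61 birth years.

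**Formula.** For reference risk p1, p2 = RR × p1, n per group and p̄ = (p1 + p2)/2:

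power = Φ{[(p2 − p1) − 1.96 √(2p̄(1 − p̄)/n)] / √([p1(1 − p1) + p2(1 − p2)]/n)}

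The least detectable RR is the value that makes this 0.80.

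**Step 1: reproduce Table 1**

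| n per group | 0.5% | 1% | 2% | 4% | 8% |
|---|---|---|---|---|---|
| 50,000, computed | 1.266 | 1.184 | 1.128 | 1.089 | 1.061 |
| 50,000, stated | 1.27 | 1.19 | 1.13 | 1.09 | 1.07 |
| 100,000, computed | 1.185 | 1.129 | 1.090 | 1.062 | 1.043 |
| 100,000, stated | 1.19 | 1.13 | 1.09 | 1.07 | 1.05 |

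Rounding the exact solutions up to two decimals gives all ten cells. A one-sided test (1.234 in the first cell) or reading N as the total (1.386) does not fit. Because the cells are rounded up, power at the stated relative risks and the table's own N is 80–90%.

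**Step 2: group size for obesity**
- 10% of 50,000 = 5,000 for one cohort; 10% of 100,000 = 10,000 for two.
- 370,000 / 61 ≈ 6,070 for one cohort; about 12,130 for two.
- Ratio of tabulated to available N: 50,000/5,000 = 10, and 50,000/6,070 ≈ 8.2.

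**Step 3: power at the stated relative risks.** Example at 2% prevalence, RR 1.13, n = 5,000: p2 − p1 = 0.0026, and both standard errors are about 0.00289. So (0.0026 − 1.96 × 0.00289)/0.00289 ≈ −1.06, and Φ(−1.06) ≈ 0.145.

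| n per group (Table 1 row used) | 0.5% | 1% | 2% | 4% | 8% |
|---|---|---|---|---|---|
| 5,000 (first) | 14.4% | 14.8% | 14.5% | 14.4% | 17.3% |
| 6,070 (first) | 16.6% | 17.0% | 16.6% | 16.6% | 20.0% |
| 10,000 (second) | 14.7% | 14.4% | 14.2% | 16.7% | 17.6% |
| 12,130 (second) | 16.9% | 16.5% | 16.4% | 19.3% | 20.5% |

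**Step 4: least detectable RR at 80% power**

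| n per group | 0.5% | 1% | 2% | 4% | 8% |
|---|---|---|---|---|---|
| 5,000 | 1.96 | 1.64 | 1.43 | 1.29 | 1.20 |
| 6,070 | 1.86 | 1.57 | 1.39 | 1.26 | 1.18 |
| 10,000 | 1.64 | 1.43 | 1.30 | 1.20 | 1.14 |
| 12,130 | 1.58 | 1.39 | 1.27 | 1.18 | 1.13 |

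**Step 5: more favourable assumptions**
- The 50,000 is a floor. Assuming 75,000 births per year (not a figure from the article), the register would hold 7,500, and power at the first-row relative risks is about 20–24%.
- Four undivided cohorts per side (20,000 to about 24,300) give about 44–61% at the first-row relative risks.

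**Step 6: continuous BMI.** With 5,000 per group, the detectable difference is 2.80 × √(2/5,000) = 0.056 SD.

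**The case against.** Several points on the other side stand.

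- A reader might infer that Table 1 is miscalculated. It is not: every cell reproduces for its stated N. The fault lies in the outcomes listed over those group sizes.
- A reader might take the worst-case description as false for obesity. In its sentence, that term refers to a dichotomous outcome of low prevalence and says nothing about group size, so the wording need not be withdrawn.
- The Discussion, under Strengths and limitations, ties 50,000–100,000 individuals to events such as fractures and T1D and does not mention obesity. The claim of strength made there is therefore not extended to obesity. Table 1 itself, however, carries no such limit.
- The article is a condensed account, and its aims cover childhood and adulthood. A further obesity source may exist in a fuller protocol. What can be said is that this article describes only the Copenhagen register.
- The seasonal analyses may pool 2–4 birth cohorts. Even four per side stay below 80% at the first-row relative risks, before any division by season.
- This is a registry study of existing records. Table 1 sets no recruitment target, and interval estimates from the fitted models will show the precision actually reached. That limits the harm but does not make the stated figures right for obesity.

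**Conclusion.** The concern holds for dichotomous obesity in the comparisons of birth cohorts before and after a change in fortification. Table 1 claims group sizes about 8 to 10 times larger than the described source can supply. With one or two cohorts per side, power at its relative risks is about 14–20.5% against a nominal 80%.

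This rests on a two-sided test, equal groups, the 50,000 floor or the register's average per birth year, and the Copenhagen register as the sole source. The article gives no obesity prevalence, so the whole tabulated range is shown. Relaxing the floor or the number of cohorts narrows the gap without closing it.

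It would go too far to conclude that the obesity component as a whole is underpowered, or that BMI must become its lead measure. The statement that BMI poses no power problem is reasonable, the linear regression is already planned, and how the obesity outcomes are ranked is a design choice that this finding does not touch. The figures for fractures and T1D are not questioned here.

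**What to change.** 1. Limit the present Table 1 rows to fractures and T1D, and remove obesity from that column heading.
2. Add obesity rows at about 5,000–6,000 and 10,000–12,000 per group, using the least detectable relative risks in step 4 of the working, and state how the group sizes follow from the register's share of each cohort. If another obesity source is to be used, name it and base the rows on its size.
3. State that a null result for dichotomous obesity cannot be read against the nationwide rows.

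The cost is a correction to one table and a few sentences. Data collection, eligibility and the planned models stay as they are. The obesity figures become less favourable.

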#### 25(OH)D3 level from DBS cards

Because the 25(OH)D3 levels in the newborn blood reflects the vitamin D status of the newborn as well as the mother at the end of pregnancy [29], measurement of 25(OH)D3 levels in DBS will serve as validation for the effect of fortification for incident cases. A control, matched for gender, exact date of birth, gestational age, being alive and with none of the aforementioned diseases will be selected and 25(OH)D3 measured. Date of birth matching criterion means that degradation of 25(OH)D3 is unlikely to bias results.

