### Statistical analyses

For the time trend analyses (i.e. to compare time to debut of a disease) of fractures and T1D, cohort analyses with all individuals born in the respective years entering the cohorts at time of birth, and the key covariates being the year/month of birth, will be conducted using Cox regression models. For the time trend analyses of obesity, similar cohort analyses will be conducted, where linear regression models will be used for the BMI as a continuous trait and logistic regression models will be used for the categorical variables (i.e. overweight and obesity), again with the year/month of birth as the key covariate. Secular trends within multiple birth cohorts used before and after change in fortification will be addressed using appropriate adjustments. Gender differences will also be considered.

Case–control analyses are envisaged for a comparison of blood spot vitamin D levels between subjects with a disease outcome and subjects who have not developed this outcome. These analyses still are based on a cohort - the entire population who has a blood spot card available, but the sampling design will be a case-cohort design, where information about the exposure will be collected only for cases developed after entry in the cohort and matched controls, randomly selected within specified strata. These data can be analysed using the Cox regression models for the event-type outcome and the logistic regression models for the dichotomous outcomes. The adjustment for possible confounders will be of particular importance in these analyses.

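### The hazard-ratio row of Table 2 implies full-cohort exposure data; with 1,000 cases and 1,000 sampled controls, power at the printed hazard ratios is about 50%, not 80%

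*Protocol article*

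**What the plan says.** Under Power calculation, Table 2 gives least detectable hazard or odds ratios "of outcome related to 1 SD difference in 25(OH)D3 for a sample size of 1000 cases and 1000 controls"; the controls are time- and gender-matched, and both rows refer to this single sample. Three scenarios are shown for the share of exposure variance explained by covariates: "no adjustment, 30% explained or 60% explained".

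- Odds-ratio row (BMI outcome): 1.13 / 1.16 / 1.22.
- Hazard-ratio row (fractures and diabetes): 1.09 / 1.11 / 1.15.

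Both rows use α = 0.05 and a power of 0.80. The article writes the power as β; the sentence for Table 1 reads "The significance level is α = 0.05 and power β = 0.80".

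The sampling is described in two other places. The section on 25(OH)D3 level from DBS cards says: "A control, matched for gender, exact date of birth, gestational age, being alive and with none of the aforementioned diseases will be selected". Statistical analyses calls the design case-cohort and says "information about the exposure will be collected only for cases developed after entry in the cohort and matched controls, randomly selected within specified strata". On the model, it adds: "These data can be analysed using the Cox regression models for the event-type outcome and the logistic regression models for the dichotomous outcomes".

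**The concern.** The two rows of Table 2 share the same 2,000 blood spots, significance level, power and covariate scenarios, yet the hazard-ratio row claims clearly smaller detectable effects. On the log scale the odds-ratio row is larger by a factor of about √2, which is what a doubling of information in the hazard-ratio row would produce. Nothing in the described sampling supplies that extra information.

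Fractures and type 1 diabetes are two of the three outcomes in the blood-spot study. The article relies on that study to validate the fortification contrast and to remove uncertainty about actual vitamin D status. If the study is believed to have 80% power at a hazard ratio of 1.09 but has about 50%, a null result would be read as stronger negative evidence than it is.

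**Working it through.** **Inputs.** From Power calculation: 1,000 cases, 1,000 controls, α = 0.05, power 0.80, R² = 0, 0.30 and 0.60, effect per 1 SD. From the DBS section and Statistical analyses: one control per case, with exposure measured only in cases and controls. Sidedness is not stated; two-sided testing reproduces the table. The multiplier is 1.960 + 0.842 = 2.8016.

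**Step 1: reproduce the printed hazard-ratio row.** For a Cox model with D events and a continuous covariate known for the whole risk set, HR = exp[2.8016 / √(D(1 − R²))]. With D = 1,000:
- R² = 0: exp(2.8016/√1000) = 1.0926 (printed 1.09)
- R² = 0.30: exp(2.8016/√700) = 1.1117 (printed 1.11)
- R² = 0.60: exp(2.8016/√400) = 1.1504 (printed 1.15)

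**Step 2: reproduce the printed odds-ratio row.** For logistic regression with N = 2,000 and half of them cases, OR = exp[2.8016 / √(N × 0.25 × (1 − R²))], that is, information 500(1 − R²):
- R² = 0: exp(2.8016/√500) = 1.1335 (printed 1.13)
- R² = 0.30: exp(2.8016/√350) = 1.1615 (printed 1.16)
- R² = 0.60: exp(2.8016/√200) = 1.2191 (printed 1.22)

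All six cells match. The hazard-ratio row uses information 1,000(1 − R²) and the odds-ratio row 500(1 − R²).

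**Step 3: information under the described sampling.** With m controls per case, a sampled-control analysis keeps m/(m + 1) of the full-cohort Cox information. For m = 1 this is 1/2, so 1,000 becomes 500. Read as case-cohort, with 1,000 controls from a large cohort with low incidence, the variance at R² = 0 is about 1/1000 + 1/1000 = 0.002, the same halving. The standard error of the log hazard ratio per SD is therefore √0.002 = 0.0447, against √0.001 = 0.0316 behind the printed row.

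**Step 4: power at the printed hazard ratios.** Power = Φ(ln HR × √(500(1 − R²)) − 1.960):

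| R² | Printed HR | ln HR × √information | Power |
|---|---|---|---|
| 0 | 1.09 | 0.0862 × 22.36 = 1.927 | 48.7% |
| 0.30 | 1.11 | 0.1044 × 18.71 = 1.952 | 49.7% |
| 0.60 | 1.15 | 0.1398 × 14.14 = 1.976 | 50.7% |

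At the unrounded hazard ratios of step 1, power is 50.8%. Over the rounding range of the printed values it lies between 45% and 53%.

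**Step 5: least detectable hazard ratios at 80% power.** With information 500(1 − R²) these are 1.1335 / 1.1615 / 1.2191, or 1.13 / 1.16 / 1.22. Keeping the printed values at 80% power would need 2 × 2.8016² / [(ln HR)² (1 − R²)] pairs: about 2,114, 2,060 and 2,010.

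**Step 6: simulation check.** With 1,000 matched pairs analysed by conditional logistic regression (4,000 replicates), power at 1.09 / 1.11 / 1.15 was 48% / 49% / 51%, and at 1.13 / 1.16 / 1.22 it was 78% / 79% / 80%. A full-cohort Cox model with 1,000 events had 79% power at a hazard ratio of 1.09, which confirms what the printed row assumes.

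**The case against.** **The formula is not named.** This is true, so the full-cohort assumption remains an inference. But all three cells match it, and 1:1 sampling does not give them: two-sided testing gives 1.13/1.16/1.22 and one-sided 1.12/1.14/1.19. If controls were pooled across the three diseases to give three per case, which the article does not say, two-sided power would still be only about 66–68%. One-sided testing with three controls per case comes close (1.095/1.115/1.154), but it contradicts the stated 1,000 controls and would not reproduce the odds-ratio row.

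**A hazard ratio can be estimated more precisely than an odds ratio.** In general it can. The printed row would be right if the 2,000 people were the entire cohort and 1,000 of them had the event. The sampling text excludes this: the cohort is everyone with a stored card, and the 1,000 controls are sampled from it.

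**The planned Cox model may itself be at fault.** A reader might infer that the stated analysis will underestimate the association. The article does not support that. It says only that Cox models can be used, which leaves room for a sampling-weighted Cox model or one stratified on matched pair, and such detail may sit in a fuller document. Only an unweighted pooled Cox model would attenuate. The amount depends on follow-up rules the article does not fix: in simulation the log hazard ratio was about 0.7 of its true value with controls followed to study end, and about 0.5 with controls censored at their case's event time. Nor would that model restore the printed power. Its standard error is about 0.0316, but on the attenuated scale; with controls followed to study end, simulated power at a true hazard ratio of 1.09 was 52%.

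**The substudy is supportive.** This also stands. Blood-spot levels are the fourth of four exposure analyses, and the fortification comparisons rest on Table 1. That limits the reach of the error but does not make the printed row right.

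**Conclusion.** The hazard-ratio row of Table 2 is wrong for the sample it describes. With 1,000 cases and 1,000 sampled controls, power at 1.09 / 1.11 / 1.15 is about 49–51% rather than 80%, and the detectable hazard ratios at 80% power are about 1.13 / 1.16 / 1.22. On the log scale the detectable effect is larger by √2, about 41%.

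This rests on two-sided testing at 0.05, one control per case (or, under the case-cohort reading, low incidence in a large cohort), and the inference about the unnamed formula. The conflict between the two rows is visible without that inference.

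The error is confined to fractures and type 1 diabetes in the blood-spot study. This point does not affect Table 1 or the odds-ratio row, although the latter uses an unmatched formula and is only approximate under individual matching. No bias in the planned Cox analysis is shown; the article simply does not say how that analysis will handle the sampling.

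**What to change.** 1. In Table 2, replace the hazard-ratio row with 1.13 / 1.16 / 1.22, or keep 1.09 / 1.11 / 1.15 and state that power is about 50%. Name the formula and the sidedness of the test.
2. Reconcile the case-cohort label under Statistical analyses with the individually matched control described under 25(OH)D3 level from DBS cards, so that one sampling design is stated.
3. Add a sentence saying that the Cox analysis accounts for the sampling, either by weighting or by stratifying on matched pair. Either can be valid if it fits the design chosen in item 2. Conditional logistic regression with risk-set sampling is one option, not the only one.

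Items 1 and 3 are corrections to a table and a sentence. Item 2 is also text, provided it records the sampling already intended; changing how controls are selected would be a design decision and is not needed to correct the power statement. The cost is a less favourable detectable effect. Keeping the printed hazard ratios at 80% power would instead take roughly 2,000–2,100 pairs, about twice the blood-spot assays.

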### Statistical analyses

For the time trend analyses (i.e. to compare time to debut of a disease) of fractures and T1D, cohort analyses with all individuals born in the respective years entering the cohorts at time of birth, and the key covariates being the year/month of birth, will be conducted using Cox regression models. For the time trend analyses of obesity, similar cohort analyses will be conducted, where linear regression models will be used for the BMI as a continuous trait and logistic regression models will be used for the categorical variables (i.e. overweight and obesity), again with the year/month of birth as the key covariate. Secular trends within multiple birth cohorts used before and after change in fortification will be addressed using appropriate adjustments. Gender differences will also be considered.

Case–control analyses are envisaged for a comparison of blood spot vitamin D levels between subjects with a disease outcome and subjects who have not developed this outcome. These analyses still are based on a cohort - the entire population who has a blood spot card available, but the sampling design will be a case-cohort design, where information about the exposure will be collected only for cases developed after entry in the cohort and matched controls, randomly selected within specified strata. These data can be analysed using the Cox regression models for the event-type outcome and the logistic regression models for the dichotomous outcomes. The adjustment for possible confounders will be of particular importance in these analyses.

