**Figure 1 F1:**
[figure not shown]
**Study cohorts. **The figure provides examples of designs for examining the effects of vitamin D fortification on development of diseases for a follow-up period of up to 50ὕyears. The birth (grey boxes with allowance for short “wash-out period” in between) and follow-up years (arrows) of individuals from subgroups exposed before and after birth are given in relation to initiation or termination of vitamin D fortification.

The study relies upon the well-defined adjacent time windows, as well as the complete registration of every citizen in Denmark via the Danish Civil registration System. Every citizen in Denmark alive April 1^st^ 1968 is assigned a civil registration (CPR) number, and this number can be used to link information, on an individual level, in the Danish birth, patient and medical registries; social and ethnic registries; and clinical and other large databases. Consequently, the study will include approx. 3 mio. individuals from nationwide birth cohorts between the 1930ies and today.

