#### Fractures

Using the CPR numbers, individuals will be individually linked to the Danish National Patient Registry for incident and recurrent diseases. The register contains information about hospital contacts, including diagnosis codes and procedure codes for all treatment received at Danish hospitals [21]; after 1994, outpatient treatment is also captured by the register. From 1977–1993, diagnoses were classified according to the WHO International Classification of Diseases (ICD-8) and from 1994 onwards according to ICD-10. The main study outcomes are fractures at wrist and hand level (ICD-8: 814–817; ICD-10: S62); fractures of forearm (ICD-8: 813; ICD-10: S52); fractures of shoulder and upper arm (ICD-8: 810–812; ICD-10: S42); and fracture of ankle (ICD-8: 824; ICD-10: S82.5, S82.6. S82.8).

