#### Perinatal exposure

Development of the disease outcomes will be compared for children born around the time when mandatory vitamin D fortification was initiated and terminated. The hypothesis is that individuals born 1–2 years after commencement of mandatory fortification (1961) and thus exposed to extra vitamin D during fetal development and for the next 24–25 years until 1985 (where fortification was ended), although unexposed thereafter, will have a lower lifetime risk of developing the aforementioned disease entities compared to individuals born 1 –2 years before fortification. Although also exposed to fortification for 24 – 25 years and unexposed thereafter, the latter group was unexposed during fetal life. Likewise, individuals born 1–2 years after mandatory fortification terminated in 1985, and who were unexposed to vitamin D both during fetal development and subsequently, will have a higher risk of later developing the diseases compared to those exposed during fetal life. Similar comparisons of disease development can be made in relation to higher exposure to vitamin D from 1972–1976, when fortified low fat milk was permitted.

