Food disappearance statistics show that margarine intake decreased and low fat milk slightly increased during the period covered. Nevertheless, changes of this nature are not expected to influence results, because the intervention group and the control group will have been born in adjacent years. Moreover, any societal changes succeeding the initiation of mandatory fortification in 1961 or its termination in 1985 may influence the intervention and control groups similarly. Thus, we find it unlikely that changes in occurrence in the outcomes associated with the introduction and cessation of fortification will lead to spurious conclusions.

We do not collect any individual data on vitamin D intake. In contrary, the individuals in the database are unselected in relation to vitamin D exposure as well as to later disease occurrence. While assuming no ecological fallacies, this in fact may be considered a very strong feature of the present study. Neither confounding from external or internal factors, nor the lack of individual data on vitamin D intake, is a prerequisite for the study, as the influences of lifestyle differences (e.g. use of infant formula, individual diet intake, use of supplements) or societal changes (e.g. in breast feeding, fortified infant formulas, sun exposure) are independent of the vitamin D intervention.

We acknowledge, however, that the differences in prenatal exposure by any subsequent age imply a more simple difference in duration of exposure. Therefore, we will conduct robustness analyses where the age scale is adjusted so that the duration of exposure becomes the same and the difference then only whether the exposure was commenced/ended prenatal or postnatal.

Moreover, there might be regional and urban/rural differences in vitamin D intake. As information on individual’s place of residence is available from Statistics Denmark, it will be included into analyses.

As diet is usually different between families with higher socioeconomic status and those with lower status [31], maternal socioeconomic status may have affected margarine/milk intake and thus exposure to vitamin D. Information on socioeconomic position, education and ethnicity is available from Statistics Denmark and can be controlled for. Adjustments will also be made for maternal age, parity, gestational age and birth weight, which is information available from the birth and patient registries and Statistics Denmark (since 1973, 1977 & 1980, respectively).

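### Entering everyone at birth in the fracture Cox model conflicts with a patient register that starts in 1977, so the unadjusted 1961 contrast gives a hazard ratio above 1 even if fortification has no effect

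*Protocol article*

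**What the plan says.** Statistical analyses fixes the Cox models for fractures and type 1 diabetes (T1D) as "cohort analyses with all individuals born in the respective years entering the cohorts at time of birth", with year and month of birth as the key covariate.

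Under Fractures, "individuals will be individually linked to the Danish National Patient Registry for incident and recurrent diseases". The same section dates the coding: "From 1977–1993, diagnoses were classified according to the WHO International Classification of Diseases" (ICD-8), with ICD-10 from 1994. It adds that "after 1994, outpatient treatment is also captured by the register". Strengths and limitations dates the sources a second time: "information available from the birth and patient registries and Statistics Denmark (since 1973, 1977 & 1980, respectively", which again puts the patient registry at 1977.

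Perinatal exposure compares births 1–2 years before and after the 1961 start and births around the 1985 end, and allows similar comparisons for the 1972–1976 milk period. Statistical analyses also promises suitable but unspecified adjustment for secular trends when several birth cohorts are used.

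**The concern.** A Cox model with age as the time scale compares people at the same age. It needs everyone counted as at risk at that age to be observable at that age. Entry at birth breaks this for people born well before 1977.

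At the 1961 switch the unexposed are the earlier-born, so they reach the start of the register about three years older than the exposed. Over those three years of age only the exposed can have an event. Fortification then appears harmful, which could hide or reverse a real benefit. The study is presented as able to detect minor effects, and its Discussion argues that comparing adjacent birth years makes spurious conclusions unlikely. For fractures, the register dates undercut that argument.

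A second, conditional issue is the addition of outpatient treatment after 1994. It falls at different ages in the compared cohorts at both switches.

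**Working it through.** **Inputs from the article.** Entry at age 0; register from 1977; outpatients after 1994 (1994.0 used; 1995 does not change the picture); births 1–2 years either side of each switch, so mean births are about three years apart; 50,000 or 100,000 per group; follow-up of up to 50 years.

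**Assumptions, not in the article.** Follow-up ends in 2012; fractures are rare enough for risk sets to stay balanced; the age shape of fracture risk; and *s*, the share of fractures recorded before outpatient capture.

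**1. The plan's own figures.** Two proportions, pooled variance, two-sided α = 0.05, 80% power. The solved relative risks are 1.266, 1.184, 1.128, 1.089 and 1.061 (50,000 per group) and 1.185, 1.129, 1.090, 1.062 and 1.043 (100,000). Rounded up to two decimals, all ten match Table 1.

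**2. 1961 contrast, no true effect, no trend adjustment.** With equal groups and rare events, the expected Cox estimate is approximately

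HR ≈ (recorded hazard of the exposed, summed over ages when both cohorts are followed) / (the same for the unexposed).

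Take mean births of 1960 (unexposed) and 1963 (exposed). Shared follow-up ends at age 2012 − 1963 = 49. The exposed are recorded from 14 and the unexposed from 17.

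- Constant hazard: (49 − 14)/(49 − 17) = 35/32 = 1.09. The full score equation at 0.004 per year gives 1.10.
- Adolescent peak: if the hazard at 14–17 is *k* times its average over 17–49, HR ≈ (3*k* + 32)/32. With *k* = 3 this is 41/32 = 1.28. Other assumed childhood or adolescent shapes gave 1.17–1.42.
- One-year windows two years apart (such as 1960 against 1962): 35/33 = 1.06 if constant, (2×3 + 33)/33 = 1.18 with *k* = 3.
- Adjacent one-year cohorts with no gap: 35/34 = 1.03 if constant; up to 1.12 in the scenarios run.

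Chance of rejecting this true null at HR 1.10, 50,000 per group, 8% prevalence (8,000 events): ln(1.10) × √8000/2 = 4.26, and Φ(4.26 − 1.96) = 0.99. At 4% it is 0.85; at 1%, 0.33.

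**3. Milk contrasts (switch dates mid-1972 and mid-1976 assumed), constant hazard.** Start: recording begins at about ages 6 and 3, so (38 − 3)/(38 − 6) = 35/32 = 1.09. End: the exposed are recorded from about age 2 and the unexposed from birth, so (34 − 2)/34 = 0.94.

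**4. 1985 contrast.** Mean births are 1984 (exposed) and 1987 (unexposed), both inside the register from birth; shared ages are 0–25. Outpatient capture starts at about age 10 and age 7. HR ≈ (10*s* + 15)/(7*s* + 18).

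| *s* | 1985 HR |
|---|---|
| 1.0 | 25/25 = 1.00 |
| 0.7 | 22/22.9 = 0.96 |
| 0.5 | 20/21.5 = 0.93 |
| 0.3 | 18/20.1 = 0.90 |

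**5. What a linear birth-date term would do.** It brings the null HR to 0.999–1.007, but exposure and birth date are nearly collinear. Variance inflation is 1 + μ²/w, where μ is the mean distance from the switch and w the variance within a window. For births 1–2 years either side: 1 + 1.5²/(1/12) = 28. For 0.5–2.5 years: 1 + 1.5²/(4/12) = 7.75. The detectable relative risk at 4% and 50,000 per group rises from 1.09 to 1.0886^√28 = 1.57, or 1.0886^√7.75 = 1.27.

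**6. The proposed remedy.** Delayed entry at 1977 alone leaves (14*s* + 18)/(17*s* + 15) at the 1961 switch: 1.00, 1.03, 1.06 and 1.10 for *s* = 1, 0.7, 0.5 and 0.3. Adding strata for the two recording periods compares ages 17–31 under the old recording and 34–49 under the new. Both cohorts then have the same recorded hazard in each stratum, so HR = 1.00 for every *s*. The same holds at 1985.

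**The case against.** The strongest reply is that the plan already promises to adjust for secular trends, and step 5 shows that one such adjustment would remove nearly all the bias. That stands to this extent: the hazard ratios above describe the unadjusted before/after comparison, not necessarily the final result. But the adjustment is unspecified and worded for several birth cohorts, while the power section also allows a single one. If it is a birth-date term, Table 1 ignores its cost. The robustness analysis in Strengths and limitations equalises duration of exposure, not register capture.

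It can also be said that delayed entry is a detail for a fuller analysis plan. Silence would be acceptable; here the article states an entry rule, and the rule does not fit the 1961 contrast.

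Three stronger readings are tempting and not supported:

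- A reader might infer that entry at birth distorts both switches, in opposite directions. At 1985 everyone is inside the register from birth. Any bias there comes only from the outpatient change, and it is nil if that change did not raise recorded fractures.
- A reader might add immortal time, because people are identifiable only if alive in April 1968. No fracture is recordable in either 1961 cohort before 1977, and ages without events contribute nothing to the partial likelihood.
- A reader might extend the point to T1D, which shares the sentence. That registry covers births since 1981, so entry at birth is right.

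**Conclusion.** The point holds for the 1961 fracture contrast, and by the same logic for milk-period contrasts whose births precede 1977. The direction at 1961 follows from the article's own dates: above 1, against the study hypothesis. The size is about 1.10 under constant hazard and about 1.28 with an assumed adolescent peak. It is 1.06–1.18 for one-year windows two years apart, and from 1.03 for adjacent years with no gap. These figures assume follow-up to 2012 and no trend adjustment. With births 1–2 years either side, even the constant-hazard value exceeds the 1.07–1.09 that Table 1 gives as detectable at 4–8% prevalence with 50,000 per group.

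For 1985 the conclusion is conditional: no bias if outpatient capture left recorded fractures unchanged, and about 0.96, 0.93 or 0.90 (towards protection) if 70%, 50% or 30% had been recorded before. The documents do not give that share.

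**What to change.** For fractures only, replace entry at birth by delayed entry at the later of birth and 1 January 1977, keeping age as the time scale. Stratify the baseline hazard by recording period, before and after the 1994 outpatient and ICD-10 change. Entry at birth can stay for T1D, and delayed entry changes nothing for births around 1985. State which secular-trend adjustment is meant; if it is a birth-date term, recalculate Table 1 with it.

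The cost is analysis wording and some precision. At the 1961 switch, ages 14–17 and 31–34 stop contributing, including part of any adolescent peak. With constant hazard and full recording, contributing years fall from 35 + 32 = 67 to 29 + 29 = 58 (13%). The standard error rises by √(67/58) = 1.07, and the detectable relative risk at 4% and 50,000 per group moves from 1.089 to about 1.096. That is far less than the cost of a birth-date term.
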